### Case identification

A list of potential eligible cases will first be identified by each ambulance Communication Centre for each month of the study period. The calls will be flagged using a combination of procedure and complaint codes for inclusivity. Dispatch platform systems differ between sites, thus, details will be outlined with each Communication Centre to ensure flagging of cases is consistent. The list will be sent to the Study Coordinating Centre in Ottawa for review.

The Coordinating Centre will cross-check each list against the CanROC list of confirmed and eligible cases for that site over the same time period. Cases will be matched using only run number and date and time of call to establish eligibility. The inclusion and exclusion criteria will be applied based on CanROC details to arrive at a monthly list of eligible cases from which data will be extracted.

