### Classification of calls

After comparing the ambulance Communication Centre and CanROC lists, each cardiac arrest case will be classified into one of the following groups:
**Confirmed, eligible:** Cases that appear on both the Communication Centre list and the CanROC list and meet the study eligibility criteria. Further data will be collected from the 9–1-1 recording and the CanROC Registry.**Confirmed, ineligible:** Cases that appear on both lists, but do not meet all study eligibility criteria. No further data will be collected from these cases.**Missed:** Cases in the CanROC registry that meet the study eligibility criteria but were not flagged by the Communication Centre. The Communication Centre will be contacted to pull these cases, and further data will be collected from the 9–1-1 recordings and the CanROC Registry.**Overcalls:** Cases that are flagged by the Communication Centre as possible OHCA cases but do not appear in the CanROC Registry. We will collect further information from the Communication Centre for these calls.

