### Sources of information

Each eligible, missed or overcalled case will be reviewed in detail using a variety of sources:
**Communication Centre:** Pre-specified quality assurance reports generated by the dispatch software in use as well as the 9–1-1 audio recordings will be available for the eligible, missed and overcalled cases. These sources will be reviewed to obtain information on key time intervals, caller/bystander characteristics, presence of agonal breathing, and details on telecommunication-assisted CPR.**CanROC Registry:** Each eligible and missed case will be linked to the CanROC Registry by run number and call date to locate standardized data that are being collected by the corresponding CanROC Sites. The CanROC minimal data set includes inputs from a variety of sources including: paramedic (ambulance) call reports, defibrillator files, fire medical assist reports, dispatch times and receiving hospital records.

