**Fig. 1 Fig1:**
[figure not shown]
Proposed data flow options

Each month during the study period, a list of potentially eligible cases will be generated by each participating Communication Centre and sent to the Study Coordinating Centre in Ottawa for classification. The Coordinating Centre will obtain a parallel list of study-eligible, confirmed cardiac arrest cases over the same time period, from the corresponding CanROC Site or the CanROC Registry. The two lists will be compared and classified into one of the four categories (eligible, ineligible, missed, overcalled). This final list of eligible cases will then be sent back to the Communication Centre for preparation. Depending on the resources available at each site, one of the following will then occur:
Study staff at each Communication Centre will locate the 9–1-1 recordings, remove all identifying information and securely transfer them to the Study Coordinating Centre in Ottawa for review. Trained study staff in Ottawa will extract the study data and enter it into the study database.Study Coordinating Centre will train local study staff to review 9–1-1 recordings, extract the study data and enter it into the study database.

The Study Coordinating Centre will adopt a pragmatic approach to accommodate possible manpower limitations, provincial regulations, privacy concerns or other issues. Where there are deviations from these processes, the revised flow will be documented.

Once the recordings have been reviewed and the required information obtained, the Study Coordinating Centre will request the CanROC variables for the eligible and missed cases.

The data will be pushed securely to the study database and will be linked via run number and call date.

Extensive steps have been taken to ensure the protection of patient privacy. At the Study Coordinating Centre, all incoming data will have been transferred securely and stripped of identifying information. No direct identifiers are included in the data being collected, information which is obtained during routine, standard care with no direct contact with research participants. De-identified electronic files will be stored securely on a network folder with access limited to essential study personnel. Paper files are stored in a locked cabinet, in a locked room.

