To obtain pooled estimates across all five regions, two methods will be used: First, we will use a random effects meta-analytical approach to pool the five region-specific intervention effect estimates and their standard errors. Next, we will use generalized linear mixed effects regression of the site-specific data with random intercepts for the sites and random slopes for time. All analyses will be conducted using SAS version 9.4 (SAS Institute, Inc., Cary, North Carolina).

#### Successful completion of telecommunication-assisted CPR instructions and frequency of CPR instructions leading to chest compressions in rare victims not in cardiac arrest – objective 3

We will use descriptive statistics with 95% CIs to describe successes in various stages of the implementation of CPR instructions (e.g. instructions offered, provided, completed, chest compressions initiated), and the frequency with which chest compressions are (rarely) going to be provided to a victim not in cardiac arrest.

#### Frequency and impact of agonal breathing on OHCA recognition by telecommunicators – objective 4

The frequency and impact of agonal breathing (proportion of missed OHCA as a result of agonal breathing) will be reported using kappa and descriptive statistics with 95% CI. Sensitivity, specificity, negative and positive predictive values will be computed with 95% CIs for the ability of ambulance telecommunicators to recognize OHCA over the telephone. OHCA recognition rates will be compared in the before and after periods using statistical analyses described above for Objectives 1 and 2.

#### Speed with which OHCA is recognized and telecommunication-assisted CPR instructions are initiated – objective 5

Descriptive statistics with 95% CIs will be used to describe various time delays occurring during telecommunication-assisted CPR instructions (e.g. time to OHCA recognition, to initiation, and to completion of instructions). We will compare these time intervals (continuous variable) in the before and after periods using statistical analyses similar to those described above for Objectives 1 and 2.

#### Objectives 6, 7, and 8

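### The planned data cannot give a valid specificity or negative predictive value for OHCA recognition, and conflicting CanROC list wording leaves PPV and the count of compressions in non-arrests open to misclassification

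*Protocol article*

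**What the plan says.** Under *Data analysis*, Objective 4, all four accuracy measures are promised: "Sensitivity, specificity, negative and positive predictive values will be computed with 95% CIs for the ability of ambulance telecommunicators to recognize OHCA".

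The calls available for this are set earlier. In *Case identification*, each Communication Centre draws up a monthly list: "The calls will be flagged using a combination of procedure and complaint codes for inclusivity". The same section notes that dispatch platforms differ between sites. *Classification of calls* then sorts cases into four groups: confirmed eligible, confirmed ineligible, missed (eligible in CanROC but not flagged) and overcalls (flagged, but they "do not appear in the CanROC Registry"). *Sources of information* limits review to three of these: "Each eligible, missed or overcalled case will be reviewed in detail using a variety of sources". The fourth group is defined as "Cases that appear on both lists, but do not meet all study eligibility criteria. No further data will be collected from these cases".

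The CanROC list used for matching is described in two ways. *Case identification* has the Coordinating Centre "cross-check each list against the CanROC list of confirmed and eligible cases for that site", and *Data management and flow* has it "obtain a parallel list of study-eligible, confirmed cardiac arrest cases over the same time period". Both describe eligible cases only. *Classification of calls* needs ineligible arrests on the list as well, and it defines overcalls by absence from the registry as a whole. The background section on CanROC says that the registry aims to hold every EMS-assessed OHCA.

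**The concern.** Specificity and NPV both need calls that were not arrests and were not taken for arrests. The protocol describes no collection or sampling of such calls, so two of the four promised measures lack a proper denominator. Any value reported would look like a property of the telecommunicators when it is a property of the flagging.

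The list conflict bears on the other side of the 2×2 table. A flagged overdose or trauma arrest has no partner on an eligible-only list. The *Confirmed, ineligible* group then cannot be filled, and the case can end up among the overcalls. That lowers PPV. It may also inflate the count of chest compressions in people not in arrest, which is the study's stated safety count. The training addresses reluctance to start CPR instructions when in doubt, so a rise in false alarms is the unwanted effect that this count should be able to show.

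**Working it through.** **Inputs from the protocol.** Table 1 gives 1,725,000 calls and 8312 eligible cases a year; summing the rows reproduces both totals exactly. The earlier multi-centre study under *Prior related work* reports 65.9% recognition, used here as an illustrative sensitivity. The protocol states no value or precision target for specificity, NPV or PPV.

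**Assumptions.** The protocol gives no number of overcalls or of flagged ineligible arrests. Ranges are shown for both.

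**Common cells.** TP = 0.659 × 8312 = 5478. FN = 8312 − 5478 = 2834.

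**Specificity = TN/(TN+FP) and NPV = TN/(TN+FN), on three readings**

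1. *Dispatch flag as the test.* Every non-arrest in the data is there because it was flagged, so TN = 0. Specificity and NPV are 0 whatever the performance.
2. *Recognition on the recording as the test.* TN is the part of the overcalls that the telecommunicator did not treat as an arrest. With 2000 overcalls, of which a share u was unrecognised, specificity = u and NPV = 2000u/(2000u + 2834):
   - u = 0.2: specificity 20%, NPV 400/3234 = 12.4%
   - u = 0.5: specificity 50%, NPV 1000/3834 = 26.1%
   - u = 0.8: specificity 80%, NPV 1600/4434 = 36.1%

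   The breadth of the codes drives the result. Take 400 false alarms. If the codes capture 2000 non-arrest calls, specificity is 1 − 400/2000 = 80%. If narrower codes capture 800, it is 1 − 400/800 = 50%. The number of false alarms is the same.
3. *All other 9-1-1 calls as negatives.* The protocol does not propose this; it is the obvious fallback. Non-arrests = 1,725,000 − 8312 = 1,716,688. With 500 to 8000 overcalls, specificity is 99.97% to 99.53%. With 2000 overcalls, NPV is 1,714,688/(1,714,688 + 8312) = 99.52% at zero recognition and 1,714,688/(1,714,688 + 2834) = 99.83% at 65.9%. Neither measure separates good performance from bad.

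**PPV = TP/(TP+FP), by treatment of ineligible arrests**

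Let F be the true non-arrests taken for arrests, and I the recognised ineligible arrests, with I = 10–50% of 5478 (548 to 2739).

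| F (assumed) | I counted as arrests: (5478+I)/(5478+I+F) | I left out: 5478/(5478+F) | I among overcalls: 5478/(5478+F+I) | Overcall pool, (F+I)/F |
|---|---|---|---|---|
| 500 | 92.3–94.3% | 91.6% | 83.9–62.8% | 2.10–6.48 |
| 2000 | 75.1–80.4% | 73.3% | 68.3–53.6% | 1.27–2.37 |
| 4000 | 60.1–67.3% | 57.8% | 54.6–44.8% | 1.14–1.68 |

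The ordering of the three PPV columns follows from the rules. The sizes follow from the assumptions.

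**Can the error be put right later in the described flow?** *Data management and flow* requests CanROC variables only for eligible and missed cases. An overcall is therefore checked through Communication Centre information and the recording, not against the registry again.

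**The case against.** **On specificity and NPV.** It is tempting to say that no true negatives exist at all. The protocol does not support that. Recognition is judged on the recording, the codes are chosen to be inclusive, and overcall recordings are available, so a flagged non-arrest that the telecommunicator did not treat as an arrest is a true negative. This stands, but it does not rescue the measures. That subset is selected by codes that may vary between sites and cannot stand for non-arrest calls in general. Nor is this a detail that a condensed article can leave to the SAP, because the described data collection does not hold the calls needed.

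**On matching.** The classification rules give ineligible arrests their own group and define overcalls against the whole registry. *Case identification* applies the eligibility criteria from CanROC details after matching, which suggests a wider starting list. *Data management and flow* itself names an ineligible category. All this is fair. The intended rule may well be the full list, but two sections say otherwise and one rule is needed.

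**On the safety count.** A reader might infer that overcalls are automatically counted as people not in arrest, so that the count is certainly inflated. The protocol nowhere equates the two, and overcalls are reviewed in detail. Inflation is possible, not shown.

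**On before/after comparison.** A reader might also infer that none is planned for compressions in non-arrests. The Objective 3 analysis is descriptive only. However, *Study design* says that the stated outcomes are compared before and after, and the stratified time-series analyses cover the outcomes of Objectives 1–5. The comparison is not spelled out, which is less than being excluded.

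**On leaving ineligible arrests out of PPV.** This is a choice of target population, consistent with the study population, and not an error in itself.

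**Conclusion.** The point holds in two parts. First, specificity and NPV as promised are not supported by the described data: they are zero by construction, or driven by flagging codes, or (with a denominator the protocol does not propose) at least 99.5% whatever the recognition rate. This part does not depend on the assumed counts. Second, *Case identification* and *Data management and flow* contradict *Classification of calls* on the CanROC list and must be reconciled. If the eligible-only list is used, PPV falls, for example from 73.3% to 68.3–53.6% with 2000 true overcalls. That fall is conditional on this reading, on the assumed counts, and on Communication Centre review not correcting the status of the cases.

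Severity is moderate. A secondary objective and the stated safety count are affected. Survival, bystander CPR and the before/after recognition rate among eligible arrests do not use these measures.

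**What to change.** - Delete specificity and NPV from the Objective 4 analysis.
- Report sensitivity as recognition on the recording among all CanROC-eligible cases, whether flagged or missed.
- Report PPV with a stated denominator that leaves confirmed-ineligible arrests out of both the true and the false positives. Counting them as recognised arrests would need their recordings, which the protocol does not collect, and paramedic-witnessed arrests were not arrests at the time of the call.
- Reword *Case identification* and *Data management and flow* so that matching uses the full CanROC list of EMS-assessed arrests, as *Classification of calls* requires, with eligibility applied afterwards.
- State that the rate of overcalls with compressions (per 1000 9-1-1 calls, for instance) will be reported before and after training, with a 95% CI for the comparison.

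The cost is protocol wording, a broader match list from the same registry, and a little more analysis. Under this PPV definition no extra recordings are needed. The list wording is best settled before cases are classified.

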#### Objectives

The overall aim of this research project is to improve the ability and speed with which ambulance telecommunicators can recognize OHCA over the phone, initiate timely CPR instructions, and improve survival for OHCA. Specific objectives are to:
Measure the impact of telecommunication-assisted CPR instructions on overall survival rates for OHCA following the implementation of an educational program on agonal breathing.Measure the impact of the educational program on overall community bystander CPR rates.Measure the frequency with which telecommunication-assisted CPR instructions are appropriately provided following the educational program.Quantify the frequency and impact of the presence of agonal breathing on OHCA recognition following the implementation of an educational program.Measure if the educational program decreases time delays before OHCA is recognized and telecommunication-assisted CPR instructions are initiated.Measure the impact of the studied community/site on OHCA recognition and OHCA outcomes.Measure the impact of the telecommunication system/platform used on OHCA recognition and OHCA outcomes.Measure the impact of telecommunicators’ training background and current local training on agonal breathing on OHCA recognition and outcomes.Identify high-quality recordings that will be used to derive a cognitive computing (IBM Watson)-assisted algorithm to rapidly recognize the presence of OHCA during conversations between 9 and 1-1 calls and telecommunicators. (Future project objective)

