We are planning pre-determined subgroup analyses to study the impact of: 6) the studied community/site; 7) the telecommunication system/platform used; and 8) the telecommunicators’ training background and current local training on agonal breathing on the previously stated primary and secondary outcomes (Objectives 1–5).

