### Data analysis

#### Overall survival to hospital discharge and community bystander CPR rates – objectives 1 and 2

Individual time series plots for each of the 5 regions will be created to visually inspect the immediate and long-term effects of the intervention, and the presence of trends, cyclical patterns, and outliers. The aggregated monthly rates in each region, expressed as percentages, will be analyzed using a simple linear segmented autoregressive model. To avoid instability due to small numerators and denominators at some sites, multiple sites within the same region will be pooled for the analysis where necessary. The model will include fixed terms for time pre-intervention, intervention, and time post-intervention. The implementation period will be censored from analysis by coding the intervention variable as missing during these months [43]. The model will be estimated using maximum likelihood estimation. Statistical significance will be obtained as the estimated beta coefficients divided by their standard errors with standard errors accounting for the autoregressive parameters. As the primary analysis will be conducted at the aggregate level, no covariates will be adjusted for in this analysis. We will assess serial autocorrelation, non-stationarity, and seasonality using the Durbin-Watson statistic, Dickey-Fuller unit root test, and visual inspection of residual plots against time. The fit of the final model will be assessed by inspecting residuals around the predicted regression lines. In case of substantial non-normality, the analysis will be conducted on the log or logit scale. The effect of the intervention will be expressed for each outcome as intercept and slope changes, where the former can be interpreted as the immediate effect of the intervention and the latter as the gradual effect of the intervention on each outcome over time. We will also evaluate the difference, at 12 months post-implementation, between the fitted post-implementation rates and the projected rates estimated using only the pre-intervention data. This represents the counterfactual effect, that is, the difference between the observed rate and the rate that would have been observed had the intervention not been implemented. We will express these differences on absolute or relative scales, with 95% confidence intervals (CI) calculated using the method of Zhang et al. [44]

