In addition to the meta-analytic (across all sites) approach proposed for the analyses of Objectives 1 and 2, we plan to stratify our interrupted time series analyses to explore the impact of 6) the studied community/site; 7) the telecommunication system/platform used; and 8) the telecommunicators’ training background and current local training on agonal breathing on the previously stated primary and secondary outcomes (Objectives 1–5).

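### Objectives 6 to 8 are assigned stratified time series with no stated between-stratum contrast, and single-site strata conflict with the plan's own reason for pooling small sites

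*Protocol article*

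**What the plan says.** The Objectives section words objective 6 as "Measure the impact of the studied community/site on OHCA recognition and OHCA outcomes", and objectives 7 and 8 ask the same of the platform and of telecommunicator training. Under Method of assessment and data collection, objectives 6 to 8 are introduced with "We are planning pre-determined subgroup analyses to study the impact of" these factors. The Data analysis section gives the method: "we plan to stratify our interrupted time series analyses to explore the impact of" site, platform and training. It places this "In addition to the meta-analytic (across all sites) approach proposed for the analyses of Objectives 1 and 2".

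The models are described in some detail:

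- Segmented model for each region: "The model will include fixed terms for time pre-intervention, intervention, and time post-intervention".
- First pooling method: "we will use a random effects meta-analytical approach to pool the five region-specific intervention effect estimates and their standard errors".
- Second pooling method: "generalized linear mixed effects regression of the site-specific data with random intercepts for the sites and random slopes for time".

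The same section combines sites within a region where needed, and gives the reason: "To avoid instability due to small numerators and denominators at some sites". The Study design section says that the design allows for sites differing both in baseline trend and in response to the intervention. The Sample size section cites a recommended 50 to 100 cases per monthly time point.

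**The concern.** Asking whether platform or training affects the response is asking about a difference between intervention effects. Separate series give one effect per stratum, each tested as its coefficient over its standard error. Unless the difference is formed, the natural reading is that a platform with a significant change responds and one without does not. That pattern arises often when the true effects are identical, especially between strata of unequal size.

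The second problem concerns objective 6. The plan pools small sites because their monthly rates are unstable. A separate survival series for each smaller Ontario centre would bring that instability back.

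At stake is the reliability of statements about which platforms or training backgrounds benefit. The Setting section says that the sites were chosen partly because they vary on these two factors.

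**Working it through.** **1. The plan's own figure.** The Sample size section gives 500 cases and 50 survivors a month. 6000/12 = 500, so the lower bound of 6000 to 7000 cases a year reproduces it. 50/500 = 10% survival, whereas the Background puts survival at rarely above 8%. Both rates are used below. No precision or power is given for objectives 6 to 8.

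**2. Terms in the stated models.** The segmented model has pre-intervention time, intervention and post-intervention time. The mixed model has random site intercepts and random time slopes. Neither has a product of intervention with platform or training, and neither lets the level change vary by site. Even if the random time slope is read to include the post-implementation trend, the level change stays common to all sites. This sits poorly with the Study design statement about differing responses.

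**3. Monthly volume at the smaller Ontario sites** (Table 1, cases a year / 12):

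| Site | Cases/month | Survivors/month at 8% | at 10% |
|---|---|---|---|
| London | 291/12 = 24.3 | 1.9 | 2.4 |
| Niagara | 250/12 = 20.8 | 1.7 | 2.1 |
| Sudbury | 134/12 = 11.2 | 0.9 | 1.1 |
| Thunder Bay | 102/12 = 8.5 | 0.7 | 0.85 |

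All four are below 50 cases a month. Ontario pooled has (1650 + 291 + 250 + 134 + 102)/12 = 2427/12 = 202.

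**4. How often equal effects look different.** Assumptions: 12 + 12 months with one transition month dropped, binomial monthly variance, no autocorrelation or overdispersion, two-sided 5% (the protocol states no alpha). The least-squares variance of the level change is then 0.758 × p(1−p)/m, where m is cases per month. At p = 10%:

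- British Columbia, m = 2800/12 = 233.3: SE = √(0.758 × 0.09/233.3) = 1.71 points; power for a 5-point change 83%.
- Ontario, m = 202.2: SE = 1.84 points; power 78%.
- Probability that exactly one is significant: 0.833 × 0.223 + 0.777 × 0.167 = 0.32.

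At p = 8% the powers are 90% and 85%, and this probability is 0.22. The same calculation gives 65% to 66% for British Columbia against Nova Scotia, and 58% to 63% for Toronto against London.

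**5. What a direct contrast gives.** The SE of a difference is √(SE₁² + SE₂²). For British Columbia against Ontario at 10%, √(1.71² + 1.84²) = 2.51 points, and the difference detectable with 80% power is (1.96 + 0.84) × 2.51 = 7.0 points. Ranges over 8% to 10% survival:

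| Contrast | Power for a 5-point difference in effect | Detectable at 80% power |
|---|---|---|
| British Columbia vs Ontario | 60% to 51% | 6.4 to 7.0 points |
| British Columbia vs Nova Scotia | 27% to 23% | 10.4 to 11.5 points |

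A five-region heterogeneity test has 56% to 47% power if the true effects are 5 points in British Columbia and Alberta and 0 elsewhere (an assumed pattern).

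**6. Are separate fits enough to form the contrast?** Yes. On simulated series, the difference between two separately fitted level changes equalled the interaction coefficient of the joint model (−1.458 both ways).

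Regions and sites stand in for strata here because the article does not say which centre uses which platform or training.

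**The case against.** The strongest reply is that this is a condensed article and the form of a subgroup comparison is commonly left to an analysis plan, which is not shown. The text says that the analyses explore, and it nowhere proposes to compare significant with non-significant strata. This limits the weight of the point. It does not remove it: the article specifies its models down to the random effects, names stratification as the method for these objectives, and says in the Objectives section that they measure impact.

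A reader might infer that the stated method cannot show whether effects differ, or leaves three objectives unanswered. The documents do not support that. Stratum estimates with standard errors are enough to form a contrast equivalent to an interaction (step 6). The random-effects meta-analysis also estimates between-region variance, which bears partly on objective 6, though not on platform or training.

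A reader might also infer that site strata undo the pooling everywhere. They do not. Prince Edward Island, with 100 cases a year, is a region by itself and has no other site to pool with. The plan pools only where needed and does not withdraw that rule for objectives 6 to 8, so ten separate series are not announced. The conflict concerns the smaller Ontario centres if objective 6 is carried out site by site.

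Finally, an explicit contrast has modest power, and adding a term does not remove confounding with site. Both are true. The gain is that an interval shows the uncertainty that side-by-side p-values conceal.

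**Conclusion.** The point holds as a low-cost improvement to exploratory secondary objectives. As written, objectives 6 to 8 produce separate series with no stated estimate of the difference in effect by platform or training, and between-group heterogeneity is addressed only across five regions. Site-level survival series for London, Niagara, Sudbury and Thunder Bay (about 24 down to 8.5 cases a month, the last with under one survivor) conflict with the plan's reason for pooling and with its cited 50 to 100 cases.

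With equal true 5-point effects, discordant significance is expected in 22% to 32% of studies for two large regions, and in about 58% to 66% for the two unequal pairs examined. These figures rest on Table 1 volumes, 8% to 10% survival, the immediate level change, an assumed two-sided 5% level, and no autocorrelation or overdispersion. Positive autocorrelation would generally lower the power figures.

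**What to change.** - **Platform and training:** report the between-stratum difference in level change and in slope change, each with a 95% confidence interval. Interaction terms in the pooled site-level model, a meta-regression, or a direct contrast of the stratum estimates would each serve. Name one.
- **Site:** add a random intervention effect to the mixed model, and report the between-site standard deviation of the effect with shrunken site estimates, instead of separate series for very small sites.
- **Interpretation:** state that platform and training vary only between 10 centres and are confounded with site, that the results are exploratory, and that significance in one stratum and not another is not evidence of a difference.

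The data are those already planned. The model is not quite the same: it gains a variance component estimated from at most 10 centres, which may be imprecise, and the intervals on the differences will be wide. If that is not acceptable, the alternative is to label objectives 6 to 8 as descriptive.
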